**Vibration Device**

The research involves investigational use of an unapproved device. This vibratory device consists of small disk that will be attached to the skin, and thus it is non-invasive. The device is operated by a 9-volt battery and there is no exposed conductive material. The output current is fused for protection. The vibrations that this device generates do not cause discomfort or pain. The device causes a slight pressure similar to the standard pulse oximeter probe; however, it should not cause long-lasting discomfort. Other tests have shown that the vibration does not interfere with sleeping patterns. The device has been reviewed and approved by the Clinical Engineering Division at UCLA, Principal Electronics Technician for the Neonatal ICU, [name] and has been deemed safe to use in human subjects.

The vibration device consists of two components: (1) small vibrating disks, which are taped to the skin over

[figure not shown]

proprioceptive fibers in the hand and foot, and (2) stimulation device containing a low voltage battery which powers the vibration motors (Figure 1). The vibration motor is similar to those found in powered toothbrushes or cell phones. The stimulation patterns are established and transmitted to the stimulation unit via Bluetooth from an Android tablet. There is no visible blue tooth connection on the device. Blue tooth signal will only be used at the start of the study to establish the parameters. This will be done remotely and away from the patient/NICU, and the Bluetooth signal will be turned off. Once the device is placed on the patient and/turned on, no Bluetooth connection exists. The android device will not be placed in the NICU by the baby's bedside. The device has been reviewed by the Clinical Engineering Division at UCLA, Principal Electronics Technician for the Neonatal ICU, [name] (under [name], Director).

The vibration devices will be attached one to the surface of the palm of the hand and one to the ankle.

The vibrator pulses in a variable-amplitude sequence designed to emulate nerve fiber discharge arising from walking or running. The vibration simulates foot movement, which increases breathing rate, even during sleep. However, while foot movement during sleep is distracting and inconvenient, mild vibratory stimulation is not. Moreover, the device is non-invasive, does not require an uncomfortable facemask for positive pressure during sleep, and does not necessitate surgery for tracheostomy for forced ventilation.

### **Analyses**

This study is a pilot study to determine effectiveness of vibratory stimulation in reducing the number and severity of breathing pauses, oxygen desaturations, and bradycardic events. A relatively small sample size ( $\leq 25$  subjects) will be used to determine effectiveness before a larger randomized-controlled trial will be conducted. The sample size may be adjusted if preliminary results are significantly different than expected (e.g. greater power). We will use within-subjects paired t-tests to assess whether significant changes occur in breathing pauses, oxygen desaturation, and/or bradycardia between periods with and without proprioceptive stimulation.

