## **Hypothesis**

Applying slight vibration to the limbs will reduce the number of breathing pauses in apnea of prematurity, thus improving the supply of oxygen to the body.

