**Exclusion Criteria:**

1. Infants with major congenital anomalies/malformations which will influence central nervous system and long-term outcomes in these infants, such as cardiac anomalies (except for PDA or VSD) or major neurological malformations, like meningoencephalocele, holoprosencephaly etc.
2. Neonates who have apnea from airway issues like laryngomalacia, tracheomalacia or severe GERD
3. Neonates with history of hypoxic ischemic encephalopathy or Grade IV IVH will be excluded

After parent/guardian consent has been obtained by the study team, the infant will be randomized by coin flip to start with or without vibration. Subjects will be monitored for 24 hours with the existing standard NICU monitors (GE HealthCare Systems). Small vibration devices will be placed on one hand and one foot. Those vibration devices will deliver continuous mild vibration in a 6 hour ON/OFF or OFF/ON sequence, for a total of 24 hours. In all subjects, we will continuously collect heart rate via 3 leads, thoracic wall movement for detection of respiratory patterns, and oxygen saturation using pulse oximetry, from the existing NICU GE HealthCare monitors. Breathing pauses [episodes >3-5 sec in duration (short pauses), and > 5sec in duration (long pauses)], IH episodes (the number of events in which O2 saturation fell below 90%, 88%, and 85% for at least 5 sec), and bradycardia episodes [occurrences of heart rate declines to less than <110 bpm (mild bradycardia), and < 100 bpm (moderate bradycardia) for at least 5 sec] will be examined. The total number and duration of breathing pauses, IH episodes and bradycardia episodes will be evaluated using LabView Software (National Instruments, Austin, TX), as well as LabChart Pro (AD Instruments), with proprioceptive stimulation (total of 12 hours) and without stimulation (total 12 hours), in each study subject.

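### The effectiveness aim rests on pauses, desaturation and/or bradycardia with no outcome given priority, although the Hypothesis names only the number of breathing pauses

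*Protocol*

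**What the plan says.** The Hypothesis section of the protocol makes one prediction: vibration "will reduce the number of breathing pauses in apnea of prematurity".

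The Analyses section is wider. It gives the aim as "This study is a pilot study to determine effectiveness of vibratory stimulation in reducing the number and severity of breathing pauses", and goes on to desaturations and bradycardic events. The method is one sentence: paired t-tests within subjects "to assess whether significant changes occur in breathing pauses, oxygen desaturation, and/or bradycardia between periods with and without proprioceptive stimulation". The three families stand side by side and none is ranked first.

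The procedures paragraph of Study Design, which follows the exclusion criteria, defines the measures:

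- Pauses come in two classes: "Breathing pauses [episodes >3-5 sec in duration (short pauses), and > 5sec in duration (long pauses".
- Desaturation is counted at three levels, as events in which saturation "fell below 90%, 88%, and 85% for at least 5 sec".
- Bradycardia has two levels, below 110 and below 100 bpm.
- For all of these, "The total number and duration of breathing pauses, IH episodes and bradycardia episodes will be evaluated using LabView Software".

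The protocol gives no significance level, no sidedness and no rule for what counts as success. It describes the study as a pilot of at most 25 infants, to be followed by a larger randomised trial.

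**The concern.** The Hypothesis and the Analyses do not match. The first is about one outcome. The second judges effectiveness on three families joined by *and/or*, each measured in several ways. Even the Hypothesis does not say whether short pauses, long pauses or both are meant.

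Without a deciding outcome, a reader of the results cannot tell which comparison was meant to carry the conclusion. A report could rest on whichever threshold or measure came out best, and nothing in the protocol would contradict it. Two things are at stake: the chance that an ineffective device is reported as effective, and the risk that an effect size picked as the best of many is carried into the planning of the larger trial.

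**Working it through.** The protocol states no error rate, so there is no figure of its own to reproduce.

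**1. Number of comparisons.** From the procedures paragraph: 2 pause classes, 3 saturation levels and 2 heart-rate levels, each by number and duration.

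(2 + 3 + 2) × 2 = 14, made up of 4 for pauses, 6 for desaturation and 4 for bradycardia.

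This count is derived. The protocol does not itself say that 14 tests will be run.

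**2. Assumptions.** Each test is two-sided at 0.05, which is 0.025 in the direction of benefit. The sample size is 25, the protocol's maximum. Vibration has no effect on any outcome. The correlations between outcomes are not given, so a range is shown.

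**3. Independent tests.**

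- Either direction: 1 − 0.95^14 = 0.512.
- Benefit only: 1 − 0.975^14 = 0.298.

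These are upper limits only. The saturation levels are nested (an event below 85% is also below 88% and 90%), as are the heart-rate levels, and number and duration describe the same events. Independence is therefore ruled out.

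**4. Correlated tests.** I simulated paired differences for 25 infants with mean zero and a 4/6/4 block correlation, 40,000 replicates per setting. For each outcome, t = mean / (SD/√25), compared with the 97.5th percentile of t on 24 degrees of freedom. The table gives the chance of at least one significant result among the 14.

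| Correlation within / between families | Either direction | Benefit only |
|---|---|---|
| 0.7 / 0.3 | 35.6% | 18.1% |
| 0.8 / 0.3 | 31.6% | 16.0% |
| 0.8 / 0.5 | 28.2% | 14.0% |
| 0.9 / 0.3 | 26.2% | 13.2% |
| 0.9 / 0.5 | 23.8% | 11.9% |
| 0.9 / 0.7 | 20.2% | 10.2% |
| One pre-named test | 5% | 2.5% |

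Benefit only: 10.2/2.5 = 4.1 to 18.1/2.5 = 7.2 times the single-test rate. Either direction: 20.2/5 = 4.0 to 35.6/5 = 7.1 times. With 10 infants the two extreme rows are little different: 36.2% and 18.7% for 0.7/0.3, 21.7% and 11.0% for 0.9/0.7.

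**5. Milder readings.**

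- All 14 tests with a common correlation of 0.95: 11.1% either direction, 5.7% benefit.
- The 7 number outcomes only, common correlation 0.7: 18.4% and 9.2%.
- One test per family (3 tests): 14.3% and 7.3% if independent; 11.0% and 5.5% at correlation 0.7.

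Each of these still exceeds twice the rate for one named test.

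**The case against.** The strongest reply is that the protocol never says that one significant result means success. The *and/or* stands in a sentence listing what the t-tests will examine. This is right: a reader might infer an any-one-of-14 success rule, but the text does not contain one. The error rates above are therefore conditional on that reading, and the 0.05 is itself assumed.

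Other stronger readings fail too:

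- A reader might call the tests unadjusted. The statistical analysis plan is not shown and could hold an adjustment or a testing order, so silence in the protocol does not establish this.
- A reader might say that a positive result triggers the larger trial. The protocol gives only the order of events, with no go/no-go criterion.
- A reader might quote 51% as the risk of a false claim. That figure needs independence, which the definitions exclude, and it counts significant worsening as well as benefit. Effectiveness here means a reduction in events, so the benefit-only figures are the relevant ones. Set against 5% instead of 2.5%, the block-correlation range of 10 to 18% is about 2 to 3.6 times.

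It can also be said that this is a small pilot, that a false positive would still face a randomised trial, and that the Hypothesis already points to one outcome. These points lower the severity. They do not remove the fault, because the Analyses section says that the study is to determine effectiveness, does so by significance tests, and does not carry the Hypothesis through. Which outcome decides is a matter for the protocol, even when details of the analysis are left to a later plan.

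**Conclusion.** The point stands as a mismatch within the protocol: a single-outcome hypothesis, and an effectiveness aim examined on up to 14 overlapping comparisons with none given priority. If a significant reduction on any of them were taken as effectiveness, the chance of a false claim of benefit would be about 10 to 18%, against 2.5% for one named test. Significance in either direction would be about 20 to 36%, against 5%. These figures rest on an assumed two-sided 0.05, 25 infants, and assumed correlations of 0.7 to 0.9 within and 0.3 to 0.7 between families. They fall if the outcomes are more strongly correlated or fewer are tested. The documents do not show a written any-one-wins rule, a confirmed lack of adjustment, or a trigger for the next trial. Given the pilot status, this is a should-fix.

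**What to change.** Before any data are examined, including any preliminary results used to reconsider the sample size, amend the Analyses section as follows:

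- Designate one primary outcome consistent with the Hypothesis: the number of breathing pauses, stimulation on versus off. The sponsor should state whether short pauses, long pauses or all pauses over 3 seconds are meant; the Hypothesis does not settle this.
- State the significance level and base the effectiveness conclusion on that test alone.
- Replace *and/or* by making desaturation, bradycardia, the other pause classes and thresholds, and all durations secondary. Report these as estimates with 95% confidence intervals, or test them in an order fixed in advance.

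With one named test, the false-positive rate returns to 5% two-sided, or 2.5% for benefit, at the assumed level. For comparison, keeping all 14 tests confirmatory under a Bonferroni correction would need 0.05/14 = 0.0036 per test, a severe demand with 25 infants.

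The cost is wording only, with no extra infants, procedures or recording time. The downside is that a lone secondary result, such as fewer desaturations without fewer pauses, could no longer support the effectiveness claim.
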